|                     |                                                                                                                                                                                                     |                       |                                        |
|---------------------|-----------------------------------------------------------------------------------------------------------------------------------------------------------------------------------------------------|-----------------------|----------------------------------------|
| Study Type   | Interventional                                                                                                                                                                                      | Clinical phase | II                                     |
| Study Design | Allocation: Randomized
Control: Active Control
Endpoint Classification: Safety/Efficacy Study
Intervention Model: Parallel Assignment
Masking: Open Label
Primary Purpose: Treatment | Project        | Miltefosine in Cutaneous Leishmaniasis |

**TITLE OF THE STUDY**

Clinical trial to assess efficacy and safety of orally administered miltefosine in Brazilian patients with cutaneous leishmaniasis and with standard care as active control

## 1. BACKGROUND

The principal species causing cutaneous leishmaniasis (CL) in Brazil is *Leishmania braziliensis* which most often leads to a cutaneous form of the disease characterized by one or more ulcers with raised borders. Approximately 3 to 5% of subjects infected with *L. braziliensis* will eventually develop mucosal disease or disseminated leishmaniasis, both considered severe forms of leishmaniasis.

Pentavalent antimony (Sbv) by intramuscular or intravenous route remains the first-line drug for the treatment of CL, a therapy that is moderately toxic and difficult to administer in poor rural areas. Miltefosine, a phosphatidylcholine analogue, is an active antileishmanial oral drug used for the treatment of visceral leishmaniasis in India. The clinical efficacy of miltefosine for New World CL was investigated in trials conducted in Central and South America. The cure rates varied from one leishmania species to another, with *L. panamensis* having 82% of cure rate, *L. mexicana* 60% and *L. braziliensis* 33% respectively. There is no data about the use of miltefosine in CL caused by *L. braziliensis* in Brazil, where this species is considered the most aggressive and prevalent agent of the disease.

## 2. OBJECTIVES

The objective of this trial is to assess if therapeutic activity and safety of oral miltefosine patients with CL caused by *L. braziliensis* in an endemic area of Bahia state is similar or superior to the standard treatment (meglumine antimoniate – Glucantime®).

Primary endpoint:

- Rate of final cures (6 month after treatment)

Secondary endpoints:

- Rate of initial cure (2 month after treatment)
- Incidence and severity of adverse events

## 3. METHODOLOGY

### 3.1 Study design

Open trial, randomized controlled phase II trial comparing miltefosine with pentavalent antimony in the treatment of cutaneous leishmaniasis.

### 3.2 Study population

It is planned to include in this study 90 patients, with 30 patients in Group 1 (2 to 12 years old) and 60 patients in Group 2 (13 to 65 years old). Of this total, 60 patients will receive the study drug (Miltefosine), while the remaining 30 will be part of the control group (receive Glucantime®). Ratio miltefosine / standard : 2/1.

#### 3.2.1 Inclusion criteria

- Newly diagnosed (untreated) cutaneous leishmaniasis with localized lesions and visualization of amastigotes in tissue samples or a positive culture or diagnosed by polymerase chain reaction (PCR) methods or by intradermal skin testing (Montenegro test)
- Number of lesions: 1 to 5 ulcerative lesions
- Lesion's diameter: 1 to 5 cm.
- Age: **Group 1: 2 to 12 years; Group 2: 13 to 65 years**
- Sex: male and female patients eligible (no effort to be made to balance the study for gender)

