##### *Evidence of infection include:*

Microscopic identification of amastigotes of *leishmania* in Giemsa staining direct (smear) and / or the demonstration of mobile promastigotes cultured aspirate and / or a biopsy of the lesion and / or by PCR identification.

The presence of parasites (the inclusion or treatment failure) is sufficiently demonstrated by a positive finding with one of three methods (swab / aspirate / biopsy) in a lesion.

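### The objective claims an effect in disease caused by L. braziliensis, but no entry route requires the species, and a skin test can be the only confirmation

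*Protocol*

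**What the plan says.** **Objective (Protocol, section 2).** The target is "patients with CL caused by *L. braziliensis* in an endemic area of Bahia state". The question is whether oral miltefosine "is similar or superior to the standard treatment", and the primary endpoint is "Rate of final cures (6 month after treatment".

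**Entry (section 3.2.1).** The patient must have new, untreated, localized cutaneous disease with 1 to 5 ulcers of 1 to 5 cm. The diagnosis must be supported by one of four alternatives: amastigotes seen in tissue, growth in culture, "or diagnosed by polymerase chain reaction (PCR) methods or by intradermal skin testing (Montenegro test". No criterion names a species.

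**Evidence of infection (section 3.4).** The list consists of smear, culture, biopsy and PCR findings. The section continues: "The presence of parasites (the inclusion or treatment failure) is sufficiently demonstrated by a positive finding with one of three methods", namely swab, aspirate or biopsy of a lesion. The skin test does not appear.

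**Background (section 1).** "The cure rates varied from one leishmania species to another". On miltefosine the rates given are 82% for L. panamensis, 60% for L. mexicana and 33% for L. braziliensis. The same section calls L. braziliensis the main species in Brazil.

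**Schedule (section 4.6).** Lesion parasitology is planned before therapy, at visit 1, and a result up to 4 weeks old is accepted. Nothing makes a positive result a condition of entry.

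**The concern.** The objective names one species, and the background presents species as something that goes with response to miltefosine. Yet the entry criteria never ask for it. They also let in a patient whose only confirmatory test is one that the Protocol does not count elsewhere as evidence of parasites in a lesion.

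What is at stake is the wording of the conclusion. A report that miltefosine is similar or superior to antimony in L. braziliensis disease would rest partly on patients in whom that species, and perhaps any parasite, was never shown. There is also a possible effect on the comparison itself. Ulcers of another cause that heal equally well in both arms would pull the arms together. In a trial whose objective can be met by similarity, that error is not conservative.

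**Working it through.** **1. The plan's own figures.** Section 3.2 gives 30 + 60 = 90 patients by age group and 60 + 30 = 90 by treatment, and 60/30 = 2, as stated. The Protocol gives no control cure rate, margin or power, so there is no further figure to reproduce.

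**2. The entry routes against sections 2 and 3.4.**

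| Route in 3.2.1 | Among the evidence of infection in 3.4? | Species required? |
|---|---|---|
| Amastigotes in tissue | yes | no |
| Culture | yes | no |
| PCR | yes | no |
| Montenegro test | no | no |

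Two separate gaps follow. The species gap covers all four routes. The parasite gap covers only the fourth.

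**3. Ulcers of another cause.** Let a fraction f have non-leishmanial ulcers with the same cure rate q in both arms. If d is the true difference, then

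observed difference = (1 - f) x d + f x (q - q) = (1 - f) x d.

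The Protocol gives neither f nor a control rate, so all of the following are assumptions: f = 10%, 20%, 30%; control 60%; q as stated. The 33% on miltefosine is the section 1 figure for L. braziliensis, so d = 33 - 60 = -27 points.

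*Power*, two-sided 5%, 30 control and 60 miltefosine patients, q from 30% to 90%:

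power = Phi{(|diff| - 1.96 x SE0) / SE1}, with SE0 from the pooled rate and SE1 from the two separate rates.

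At f = 0: pooled rate (0.60 x 30 + 0.33 x 60)/90 = 0.42; SE0 = sqrt(0.42 x 0.58 x (1/30 + 1/60)) = 0.110; SE1 = sqrt(0.60 x 0.40/30 + 0.33 x 0.67/60) = 0.108; power = Phi(0.50) = 69%.

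*False finding of similarity*, with a further set of assumptions (control 60%, true miltefosine rate 45%, margin 15 points, one-sided 2.5%, q of 50% or 90%):

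P = Phi{(15 - diff)/SE - 1.96}, where diff = (1 - f) x 15 points and SE is taken on the same scale.

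| f (assumed) | -27 points becomes | Power | False similarity |
|---|---|---|---|
| 0 | -27.0 | 69% | 2.5% |
| 10% | -24.3 | 59-60% | 3.4% |
| 20% | -21.6 | 49-51% | about 4.6% |
| 30% | -18.9 | 39-41% | 6.0-6.3% |

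**4. Other species.** Taking the section 1 rates at an assumed f = 20%, the miltefosine arm would rise from 33% to 0.8 x 33 + 0.2 x 60 = 38.4% (L. mexicana) or 0.8 x 33 + 0.2 x 82 = 42.8% (L. panamensis). That is one arm only. With control rates c1 for L. braziliensis and c2 for the other species, the between-arm difference changes by

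f x [(m2 - c2) - (33 - c1)] = f x [(m2 - 33) - (c2 - c1)].

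For m2 = 60 the sign turns on whether control does better in the other species by more than 27 points; for m2 = 82, by more than 49. The Protocol gives neither c1 nor c2, and does not say which other species occur in the study area, so the direction cannot be fixed.

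**The case against.** The strongest case against the point has five parts.

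- **The skin test does not stand on its own.** It supports a clinical diagnosis of ulcerative disease in an endemic area where section 1 makes L. braziliensis the leading species. Many such patients may well have it. This stands, and it is why no size can be claimed.
- **Randomisation protects the comparison.** Entry is decided before allocation by the same criteria in both arms, so the comparison is fair for the patients enrolled. This stands too. The problem is which population the result describes.
- **Section 3.4 is not an entry rule.** A reader might infer that it contradicts section 3.2.1 by demanding parasites at inclusion. It does not. It says when their presence counts as demonstrated. But it mentions inclusion and leaves out one of the four routes, so the two sections need a linking sentence.
- **The skin test is not the cause of the species mismatch.** A reader might infer that dropping it would align entry with the objective. It would not, because smear, culture and PCR as written do not require species either.
- **A confirmed-case analysis is often left to a SAP.** That is so, and its absence from the Protocol is no fault. But the objective and the entry criteria belong to the Protocol, and a SAP cannot reconcile them. The title and section 3.1 already speak of cutaneous leishmaniasis without a species, so the remedy is largely one of wording.

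**Conclusion.** The point holds as a mismatch between the claim and the population. Section 2 names a species that no entry route in section 3.2.1 requires, and a patient can be eligible with no parasite shown in a lesion. As written, the trial can support a conclusion about cutaneous leishmaniasis where L. braziliensis is endemic, but not one about disease shown to be caused by it.

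It would go too far to say that the comparison is diluted. That depends on how many patients enter on the skin test only and how many of those have another disease, and the Protocol gives neither. All that follows is conditional: a fraction f of non-leishmanial ulcers healing alike in both arms multiplies the difference by (1 - f), which works against superiority and towards similarity. The power and error figures above also rest on assumed control rates and an assumed margin. Nor does the 82% rate for L. panamensis show that the comparison is inflated. It concerns the miltefosine arm only, and the Protocol does not place that species in Bahia.

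This should be corrected, because it changes what may be concluded. It does not invalidate the design.

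**What to change.** 1. **Reconcile sections 2, 3.2.1 and 3.4.** Say plainly whether a positive skin test may be the only confirmation, and how that fits the text on demonstrating parasites at inclusion.
2. **Reword the objective, and the conclusion to be drawn,** to cutaneous leishmaniasis in an area of Bahia endemic for L. braziliensis, unless species is identified.
3. **Keep all randomised patients in the primary analysis,** so that the randomised comparison is preserved.
4. **Pre-specify one supportive analysis,** in the Protocol or the SAP: the same comparison in patients with a positive smear, culture or PCR at visit 1. Record which test confirmed each patient and report the numbers by arm, so that the skin-test-only share is known.

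**Cost.** Changes of wording and one extra analysis, using lesion parasitology that section 4.6 already schedules. The price is a more modest claim about species, and a confirmed subset smaller than 90 with a correspondingly wider interval. A conclusion tied to L. braziliensis itself would need species typing, which no visit schedules; that would be an added procedure and is not part of this recommendation.

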#### 3.2.2 Exclusion criteria

*Safety concerns:*

- Thrombocyte count  $<30 \times 10^9/l$
- Leukocyte count  $<1 \times 10^9/l$
- Hemoglobin  $<5 \text{ g}/100 \text{ ml}$
- ASAT, ALAT, AP  $\geq 3$  times upper limit of normal range
- Bilirubin  $\geq 2$  times upper limit of normal range
- Serum creatinine or BUN  $\geq 1.5$  times upper limit of normal range
- Evidence of serious underlying disease (cardiac, renal, hepatic or pulmonary)
- Immunodeficiency or antibody to HIV
- Severe protein and/or caloric malnutrition (Kwashiorkor, Marasmus).
- Any non-compensated or uncontrolled condition, such as active tuberculosis, malignant disease, severe malaria, HIV, or other major infectious diseases
- Lactation, pregnancy (to be determined by adequate test) or inadequate contraception in females of childbearing potential for treatment period plus 2 months

*Lack of suitability for the trial:*

- Any history of prior anti-leishmania therapy
- Any condition which compromises ability to comply with the study procedures
- Concomitant serious infection other than cutaneous

*Administrative reasons:*

- Lack of ability or willingness to give informed consent (patient and/or parent / legal representative)
- Anticipated non-availability for study visits/procedures

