### 3.2.3 Criteria for withdrawal

A premature withdrawal or discontinuance shall be construed as withdrawal procedures of the study after the first exposure to study treatment. Withdrawals before that time should be considered "failures of selection."

Patients may be withdrawn from the study at any time at its own request or on the basis of clinical trial investigator. However, patients who request the withdrawal will be strongly encouraged to conduct appropriate tests to make a valid assessment and possible inclusion in the analysis.

The reasons for withdrawal are classified as follows:

**Lack of effectiveness:** The patient showed inadequate response to treatment or deterioration.

**Lack of tolerance:** the dose-limiting intolerance reported by patients or observed by the doctor and found to be "probably" related to study treatment (and therefore does not refer to an aggravation of a preexisting condition).

An adverse event is considered dose limiting toxicity if he understands grade 3 or 4 of the common terminology criteria for adverse events (CTCAE) and is confirmed by a re-assessment within a week.

In the case of treatment of grade 3 transaminase elevation CTCAE, the investigator may decide to continue treatment until no manifestation of liver injury is observed (eg. Jaundice), additional control tests are designed to ensure patient safety.

The CTCAE grade 4 elevation of enzyme (s) impairment (s) or clinical signs of liver damage require immediate discontinuation of study treatment.

**Intercurrent disease:** A disease or condition that occurred or worsened during the study and prevented the completion of treatment and procedures of the study, however, no evidence of a causal relationship to study treatment, the adverse event record corresponding to classify causality as "unlikely" or "not assessable".

**Withdrawal of consent / non-adherence:** The patient, parent or legal guardian withdrew consent or the patient did not adhere to study procedures (must be verified if an adverse event caused withdrawal).

**Other (s) reason (s):** Reason for discontinuation not approached by any of the criteria above, p. ex., moving the patient, other reasons must be specified.

Patients who are withdrawn from the study will not be replaced.

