#### Modifications in the treatment

Reduce dose: A patient who does not tolerate the dose of Miltefosine used, will leave the treatment. No dose reduction is planned.

Discontinuation of study treatment: The criteria for withdrawal are presented in section 4.2.3.

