## **4. STUDY PROCEDURES**

### **4.1 Pre-study evaluation / selection**

Before the first administration of study medication, the investigator will inform the patient verbally and in writing about the potential benefits and any risks associated with their participation in this study and obtain a consent in writing.

The assessment team to verify compliance with the criteria for inclusion / exclusion include:

**Medical history:** General medical history (demographic data, sensitivity to medications and allergies, medical history and surgical significance), concomitant medication, history of leishmaniasis, previous treatments

**Physical examination:** Will be recorded: blood pressure, pulse, weight, height, temperature.

**Medical laboratory tests \*** CBC (no differential), platelets, stool examination  
HIV serology by ELISA or rapid test  
Biochemistry (Na+, K+, urea, creatinine, ALT, AST, LDH, alkaline phosphatase)  
Urinalysis (record of blood and protein only)  
Pregnancy test:  $\beta$ -HCG serum  
Hepatitis C antibodies, HBsAg, anti HBc

\*) All laboratory studies conducted in laboratory validated and reviewed. Abnormal values (values outside the normal laboratory values - 3 benchmarks) will be specifically addressed in patient records.

A second evaluation (at baseline) to verify adherence to the criteria for inclusion / exclusion will be necessary if the time between the assessment team and the first administration of study medication more than two weeks. Include the variables as above for the assessment of selection. In a female patient that requires a waiting period for repayment of a pregnancy test, to repeat the screening tests is unnecessary in the absence of clinical deterioration.

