#### *Variable security:*

Vital parameters

Adverse Events

Laboratory tests (CBC, clinical biochemistry, urine)

Pregnancy test in women who may become pregnant

*Overall assessment:* Reason for discontinuation, overall assessment of tolerability  
A variation of the assessments plus / minus 2 days is acceptable. If these variations are not met, the reason should be documented in the appropriate page of medical records.

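### The blood-count exclusion limits admit patients who, on the usual CTCAE bands, already stand at grade 3 or worse, so reaching grade 3 cannot mark a new toxicity for that count

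*Protocol*

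**What the plan says.** Three parts of the protocol bear on this.

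- **Entry.** The safety exclusions in section 3.2.2 begin with "Thrombocyte count $<30 \times 10^9/l", followed by leukocytes below 1 x 10^9/l and haemoglobin below 5 g/100 ml. Anyone at or above these values passes on blood counts. The counts are known before treatment, because section 4.1 lists "CBC (no differential), platelets, stool examination" at selection.
- **Toxicity.** Section 3.2.3, under lack of tolerance, reads "An adverse event is considered dose limiting toxicity if he understands grade 3 or 4 of the common terminology criteria", and asks for confirmation within a week. The grade itself is absolute. The same heading requires a probable relation to treatment and sets aside the worsening of something the patient already had. Section 3.3.3 (Modifications in the treatment) adds "A patient who does not tolerate the dose of Miltefosine used, will leave the treatment. No dose reduction is planned".
- **Laboratory values.** Section 3.4 (Documentation of security parameters for routine) sends an out-of-range value to the adverse event form only if the investigator finds it of major relevance: it is serious, it made the patient stop early, or it had to be treated. CTCAE grade is not part of that test. Sections 4.2 and 4.3 schedule a CBC on days 7, 14 and 21 and at the end of treatment.

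**The concern.** A toxicity threshold works best when patients start on the safe side of it, because crossing it is then news. If the entry limits lie beyond the threshold, some patients start on the wrong side. For that count, reaching grade 3 says nothing about what the drug has done. The grade is the only numeric trigger that the protocol prints for a blood-count toxicity, and miltefosine has no reduced dose to fall back on. For such a patient, who could be a child from age 2 (section 3.2), the choice between continuing and stopping rests on causality assessment and discretion until the count falls a full grade further.

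**Working it through.** **Inputs from the protocol.** Exclusion limits of 30, 1 and 5 (section 3.2.2); 90 patients, 60 of them on miltefosine (section 3.2); CBC on days 7, 14, 21 and 28 (sections 4.2 and 4.3), so four readings after the start of treatment.

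**Inputs assumed.** The protocol gives neither the CTCAE bands nor the share of patients with low counts. Usual bands: grade 3 starts below platelets 50, leukocytes 2 and haemoglobin 8; grade 4 starts below 25, 1 and 6.5. Prevalence p: 0.1% to 2%.

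**Step 1: overlap.** Width = start of grade 3 minus exclusion limit. The middle case takes the midpoints between the limits and the usual bands, only to show how the result depends on the assumption.

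| Grade 3 starts below (platelets / leukocytes / Hb) | Platelets | Leukocytes | Haemoglobin |
|---|---|---|---|
| 50 / 2 / 8 | 50 - 30 = 20 | 2 - 1 = 1 | 8 - 5 = 3 |
| 40 / 1.5 / 6.5 | 40 - 30 = 10 | 1.5 - 1 = 0.5 | 6.5 - 5 = 1.5 |
| 30 / 1 / 5 | 0 | 0 | 0 |

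The overlap disappears for all three counts only if grade 3 starts no higher than 30, 1 and 5.

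**Step 2: what the grade can still show.** On the usual bands, every patient in the platelet and leukocyte overlaps enters at grade 3, because 30 is above 25 and 1 is not below 1. Such a patient can still move visibly to grade 4. From platelets of 45 that takes a fall to below 25, that is, of more than (45 - 25)/45 = 44%. A fall from 45 to 32 is 13/45 = 29% and stays in grade 3, the same grade as a count that never moves. For haemoglobin, 6.5 to 7.9 enters at grade 3, but 5.0 to 6.4 enters at grade 4, with no higher grade left within the 3-4 band.

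**Step 3: confirmation.** Days 7 and 14 are one week apart. A stable count of 45 and a count that has fallen to 32 and stays there both read grade 3 on repeat, so confirmation does not separate them.

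**Step 4: how many patients.** Expected number = n x p; chance of at least one = 1 - (1 - p)^n.

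| p | Expected of 90 | At least one of 90 | Expected of 60 on miltefosine | At least one of 60 |
|---|---|---|---|---|
| 0.1% | 0.09 | 9% | 0.06 | 6% |
| 0.5% | 0.45 | 36% | 0.3 | 26% |
| 1% | 0.9 | 60% | 0.6 | 45% |
| 2% | 1.8 | 84% | 1.2 | 70% |

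The low end is more plausible. The disease is localised, and section 3.2.2 also excludes serious underlying disease, immunodeficiency, severe malnutrition and malignancy.

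**The case against.** The protocol has safeguards, and they answer several stronger readings.

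- *The rule takes no account of baseline.* A reader might infer this from the absolute grade. But lack of tolerance requires a probable relation to treatment and leaves out pre-existing conditions, and the relevance test in section 3.4 keeps a stable low count off the adverse event form unless it is serious, stops treatment or needs treating. An unchanged platelet count of 45 is therefore not called dose limiting four times over. This stands.
- *The grade is useless for these patients.* It is not. Step 2 shows that a fall into grade 4 is visible for platelets, leukocytes and part of the haemoglobin range, and the rule works as intended for every other toxicity. This stands too.
- *There is no way to withdraw or code such a patient.* There is. "Patients may be withdrawn from the study at any time" covers investigator discretion, a probably related fall can be recorded as lack of tolerance, and there is a residual category: "Reason for discontinuation not approached by any of the criteria above".

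Harm also needs a rare patient, a drug-related fall within one grade, and an investigator who does not act on weekly counts. Section 5.2 does not list blood counts among miltefosine's main adverse effects. The title of reference 8 speaks of rising leukocyte and platelet counts with this compound, though it says nothing about haemoglobin.

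Finally, any limit has an edge. With 50 as the limit, a change from 51 to 49 (2/51 = 4%) would read as new grade 3, and judgement would still be needed.

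What remains is narrower. The safeguards prevent a stable low count from being counted, but they do not identify a worsening one. The pre-existing-condition wording could even be read as leaving it out, and a test that asks whether a value led to stopping cannot tell the investigator when to stop.

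**Conclusion.** The point holds as a cheap improvement on patient safety, with medium confidence. On the usual CTCAE bands, all three limits admit patients already at grade 3 or, for haemoglobin below 6.5, grade 4. For that count, reaching grade 3 cannot mark a new toxicity, and a worsening within the grade is left to the investigator. It probably touches fewer than one of the 90 patients: the expected number stays below one for any prevalence under 1/90 = 1.1%.

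The conclusion rests on the assumed bands and disappears if grade 3 starts at or below 30, 1 and 5. The prevalence is also assumed. A reader might infer an effect on the cure rates at 2 or 6 months. Nothing in the protocol supports that, since cure is judged on healing of the ulcers and at most a patient or two would be affected over the assumed range.

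**What to change.** Raise the three exclusion limits in section 3.2.2 to the start of grade 3 in the CTCAE version that the trial uses. Under the assumption made here, that means excluding platelets below 50 x 10^9/l, leukocytes below 2 x 10^9/l and haemoglobin below 8 g/100 ml, subject to the sponsor's clinicians. Leave the rule in section 3.2.3 as it is. Any grade 3 or 4 count on treatment is then new relative to entry, and the existing rule catches it.

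The cost is three numbers. No test is added, because the CBC and platelets are already part of selection. The loss is 0.09 to 1.8 otherwise eligible patients per 90 over the assumed range. They would be screened out before treatment, so others can be enrolled to reach the planned 90.
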